### Sample size

2.4

This RCT will be conducted in two sequential phases. The first phase serves as a pilot study aiming to obtain preliminary estimates of the intervention’s effect size, variability, and feasibility parameters. These pilot data will provide empirical inputs for calculating the appropriate sample size required for the subsequent full-scale RCT.

In this pilot phase, the primary objective is not hypothesis testing but to estimate outcome variance and effect size with sufficient precision to inform future sample size determination. Following commonly recommended practices for pilot RCTs (17), approximately 25 participants per group (about 50 in total) will be recruited. Considering an anticipated 10%–20% attrition rate, the total recruitment target is set at 60 participants (30 per group).

The effect size derived from this pilot phase will then be used to conduct a formal power analysis to determine the optimal sample size for the main RCT, ensuring adequate statistical power to test the study hypotheses.

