### Statistical analysis

2.11

We will collect quantitative data using a structured questionnaire and then input it into Microsoft Excel for analysis. All major analyses will follow intention to treat (ITT) and will undergo protocol compliant (PP) analysis for sensitivity testing. Descriptive statistics will be used to summarize feasibility variables such as starting information, number of participants, and system usage. For continuous data, the mean and standard deviation of normally distributed data, as well as the median and 25th to 75th percentile of non-parametric data, will be provided. To compare the untreated group and the group measured once, independent sample *t*-tests and their non-parametric analogues will be used. The categorical data will be expressed in frequency and percentage, and analyzed using chi square test. The normality of the data will be tested using the Kolmogorov Smirnov test. Under the assumption of random missing data, established multiple imputation methods will be used in appropriate circumstances to handle the missing data. We will examine and compare the missing and wear patterns between each group to identify potential differences in dropout rates, and conduct sensitivity analysis to compare estimated and complete case outcomes. For the main experiments, the focus will be on using a linear mixed effects model to evaluate the main outcome indicators. For secondary outcomes such as self-management and psychosocial/cognitive outcomes, analysis will use similar mixed effects models or simpler comparison methods, depending on the nature and timing of data collection. In addition, exploratory age stratification analysis can be conducted to examine the potential heterogeneity of intervention effects across different age groups in a descriptive manner. Given the pilot nature of the study, the results should be interpreted with caution. The measurement criteria used by the system, such as the number of questions, will be summarized in a descriptive manner and can be included as covariates in exploratory analysis to better understand compliance patterns; these analyses will be seen as hypothesis generation rather than validation. All statistical tests are two-sided, with a significance level of 0.05. Data analysis will be conducted using IBM SPSS Statistics (version 24.0; SPSS Inc., Chicago, Illinois, USA and Stata (version 14.0); StataCorp, College Station, TX, The United States) conducted.

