## Discussion

5

This study is designed to systematically evaluate the effectiveness of the AI-HEALS intervention, delivered via the WeChat platform, in improving physiological indicators, mental health, and self-management behaviors among patients with COPD through a randomized controlled trial. Although previous interventions have provided some benefits for patients with COPD, long-term self-management remains challenging due to the complexity of the disease, psychological burden, and limited access to continuous, individualized support (9, 10). Existing mobile health interventions have attempted to address these issues. However, their effectiveness has often been constrained by high dropout rates, complex intervention procedures, or a narrow focus on selected behavioral outcomes (12, 13).

Against this backdrop, the present study integrates a 3-months AI-HEALS intervention grounded in the HAPA-MTM framework with a 9-months follow-up period to evaluate both the effectiveness and sustainability of behavior change. The use of artificial intelligence enables the delivery of tailored, timely, and scalable health education, while the integration with WeChat, a widely adopted communication platform, may enhance accessibility and user engagement. By addressing gaps in the literature regarding the long-term sustainability and practicality of digital self-management interventions for COPD, this study aims to contribute empirical evidence supporting the role of AI-enabled tools in chronic disease management.

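### The main RCT is to be sized on the effect observed in a pilot of about 25 per group, which estimates the SD usefully but the effect too imprecisely to set a sample size

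*Protocol article*

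**What the plan says.** Section 2.4 (Sample size) describes one RCT in two sequential phases. The pilot is not meant to test hypotheses. Its objective is "to estimate outcome variance and effect size with sufficient precision to inform future sample size determination". On the basis of common pilot practice, "approximately 25 participants per group (about 50 in total) will be recruited", and after an allowance for attrition "the total recruitment target is set at 60 participants (30 per group").

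The section then fixes how the second phase will be sized: "The effect size derived from this pilot phase will then be used to conduct a formal power analysis to determine the optimal sample size". This refers to the main RCT, and the stated purpose is "ensuring adequate statistical power to test the study hypotheses".

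Section 2.8.1 makes change in CAT score the primary outcome. Neither that section, section 2.4 nor section 2.11 names a target CAT difference, an SD, a precision criterion for the pilot, or any rule (a confidence limit or shrinkage) that would temper the observed effect before it is used. Section 2.11 sets the error rate: "All statistical tests are two-sided, with a significance level of 0.05".

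**The concern.** The plan treats the variance and the effect as equally well estimated by the same 50 or so patients, and they are not. A pooled SD on 48 degrees of freedom is moderately precise. A standardized mean difference from the same data is not, and the required sample size depends on the inverse square of that difference, so its error is magnified.

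If the pilot estimate is high by chance, the main RCT will be too small to detect the real effect. If it is low by chance, the main RCT will be needlessly large or will be abandoned. Either way, chance in the pilot would largely decide the size of the confirmatory trial, although the plan presents that size as optimal and adequately powered.

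**Working it through.** **Inputs from the protocol article.** About 25 evaluable per group, 60 recruited, attrition 10%–20% (section 2.4); 1:1 allocation (section 2.2); two-sided alpha 0.05 (section 2.11); continuous primary outcome, change in CAT (section 2.8.1).

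**Assumptions, because the document gives no figure.** Power 80%; true standardized effect d of 0.3, 0.4 or 0.5; a simple unadjusted two-group comparison unless stated otherwise.

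**1. The plan's own figure.** 50/(1 − 0.10) = 55.6, so 56; 50/(1 − 0.20) = 62.5, so 63. The target of 60 lies inside this range and matches attrition of 16.7%. At 20% attrition, 60 × 0.80 = 48 remain, or 24 per group. The pilot target is reproduced and is not at fault.

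**2. Precision of the SD.** With 48 df the 95% limits are √(48/χ²) at the two chi-square quantiles, giving 0.83 to 1.25 times the estimate. For a fixed target difference the sample size is proportional to SD², so it moves by a factor of 0.83² = 0.69 to 1.25² = 1.56. That is usable.

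**3. Precision of the effect.** SE(d) ≈ √(2/25) = 0.283, so the half-width is 1.96 × 0.283 = 0.55 SD (0.57 at 24 per group, 0.51 at 30). Exact noncentral-t 95% intervals at 25 per group, and main-trial n per arm from 2(1.96 + 0.84)²/d²:

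| Observed d | 95% CI | n per arm at estimate | n per arm at upper limit | n per arm at lower limit |
|---|---|---|---|---|
| 0.3 | −0.26 to 0.86 | 175 | 22 | undefined |
| 0.4 | −0.16 to 0.96 | 99 | 18 | undefined |
| 0.5 | −0.07 to 1.06 | 63 | 14 | undefined |
| 0.8 | 0.22 to 1.37 | 25 | 9 | 327 |

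**4. What the rule delivers.** 200,000 pilots were simulated at each assumed true d. In each, the observed d came from 25 per group with an SD on 48 df, the main trial was sized at n = 2(1.96 + 0.84)²/d² using that observed d, and true power was computed as Φ(d√(n/2) − 1.96) using the true d. The size columns apply when the estimate is positive. The last two columns are shares of all pilots.

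| True d | n per arm needed | 10th–90th percentile of n | Estimate ≤ 0 | True power < 50%, further share |
|---|---|---|---|---|
| 0.3 | 175 | 32 to 1,887 | 14% | 0.381 × 0.856 = 33% |
| 0.4 | 99 | 25 to about 900 | 8% | 0.302 × 0.921 = 28% |
| 0.5 | 63 | 20 to 438 | 4% | 0.235 × 0.961 = 23% |

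Check by hand at d = 0.4: the estimate is ≤ 0 with probability Φ(−0.4/0.283) = Φ(−1.41) = 8%. True power falls below 50% when the observed d exceeds 0.4 × 2.80/1.96 = 0.57, which has probability about 1 − Φ(0.17/0.283) = 27%. Both agree with the simulation. As a single example, an observed 0.8 gives 25 per arm, and true power is then Φ(0.4 × √12.5 − 1.96) = Φ(−0.55) = 29%.

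**5. With baseline adjustment.** The half-width becomes 0.55 × √(1 − ρ²): about 0.48 SD at an assumed correlation ρ = 0.5 and about 0.40 SD at ρ = 0.7. At a true d of 0.4 the main trial then needs 74 or 51 per arm. The 10th–90th percentile is 22 to about 575 or 18 to about 295, the estimate is ≤ 0 in about 5% or 2% of pilots, and true power is below 50% in a further 25% or 20%.

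**The case against.** Several points can fairly be made for the plan.

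- **The pilot size is conventional.** This stands. Twenty-five per group is reasonable for the SD, attrition and feasibility. The fault lies only in how the observed effect is used.
- **The primary analysis is a mixed model, which will be more precise than a plain comparison.** This stands in part. Step 5 shows that the spread narrows, but a fifth to a quarter of pilots would still lead to a main trial with less than 50% power. The figure of about 900 per arm is an unadjusted one and should be read as such.
- **The effect can still be estimated.** Yes, but imprecisely, and the interval does not always include zero: at an observed 0.8 it is 0.22 to 1.37. Even then the implied size runs from 9 to 327 per arm.
- **No main-trial size has been fixed, and amendments go through committee review (section 3.1).** True, so the fault does not harm the pilot. But section 2.4 already commits to the method, and a target difference chosen after the pilot effect is known loses its independence from the data.
- **Section 2.11 asks for caution given the pilot nature of the study.** That concerns interpreting results and leaves the sizing rule unchanged.

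Two stronger readings are tempting but not supported. A reader might infer that the pilot is being run as an efficacy test, since the Discussion says the study is designed "to systematically evaluate the effectiveness of the AI-HEALS intervention" and section 2.11 applies a 0.05 level. But section 2.4 describes a two-phase RCT, so those statements can refer to the whole programme. A reader might also infer that pilot patients will be pooled into the main analysis; nothing in the document says so.

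**Conclusion.** The concern holds for section 2.4. The precision claim is roughly right for the SD and wrong for the effect, and sizing the main RCT on the observed effect does not deliver the power that the section promises. Under the stated assumptions with a true d of 0.4, about 8% + 28% = 36% of pilots end either with no usable estimate or with a main trial whose true power is below 50%. The corresponding totals are 14% + 33% = 47% at d = 0.3 and 4% + 23% = 27% at d = 0.5.

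The exact sizes rest on the assumed effects, on 80% power and on an unadjusted comparison, none of which the document states. The direction survives baseline adjustment with correlations of 0.5 to 0.7. The conclusion concerns the rule for the second phase, not the validity or size of the pilot.

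**What to change.** In section 2.4:

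1. Replace the sizing sentence. Power the main RCT to detect a between-arm CAT difference judged important, named and fixed before any pilot results by arm are seen, and state the power level.
2. Take from the pilot only the SD, the correlation between baseline and follow-up CAT, and the recruitment and attrition rates. Preferably allow for uncertainty in the SD; a one-sided 80% upper limit, about 1.10 times the estimate, is one option.
3. Remove the effect size from the precision claim, leaving the variance.
4. Say that the pilot CAT difference will be reported as an estimate with its confidence interval.

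The cost is wording only, with no extra pilot patients and no change to the target of 60. The main-trial size that results may be less favourable than one based on an encouraging pilot effect.

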### Recruitment

2.5

This study aims at enrolling participants who qualify for inclusion and exclusion in the target hospital. Recruitment will be performed by the medical staff of the hospital, which will screen eligible patients upon their discharge or admitting them to extend their invites. Next, an initial personal contact with patients will be made by the research team, whose study’s purpose, procedures involved, probable gains, and possible risks will be explained in details. Eligible patients will be invited to their respective hospitals for a comprehensive health evaluation, which includes an in-depth review of the history of COPD, and symptoms. Upon ensuring that patients understand the study completely by answering their questions, participants will be asked to sign an approved consent document. Participants that have signed an approved consent document will be officially enrolled in a study. Apart from this, we will use a consistent measurement proxy to make sure that measurements by self-report are reliable.

### Informed consent

2.6

The process of informed consent will be done openly and transparently, adhering strictly to ethics. Participants meeting inclusion and exclusion criteria will be given a detailed written document describing the aims of the study, procedures, possible hazards and gains, and measures for protecting their information. It also includes explicit details of their information being collected, stored, and secured. We will keep all data securely encrypted on secured servers, accessible only by authorized members of our research team during the study, and properly disposed of after study completion. Participants will have sufficient time to read carefully through the consent document, request any questions, and provide consent voluntarily. Participants will be clearly informed that they can withdraw from the study at any point without any adverse consequences. We will offer continuous points of contact for consultations so that participants can seek additional information or clarifications if required. During the study, we will make all new information available to participants that could change their decision to remain in the study, ensuring continuous informed consent.

In addition, individuals who withdraw from the intervention group will not be penalized. Where intervention is underway, patients who withdraw cannot be reassigned to the control arm and will be counted as a natural attrition case. Semi-structured interviews with patients who withdraw, where possible, will be conducted to learn about their reasons for withdrawal. Participants will be made explicitly informed of all possible options upon withdrawal at the point of informed consent, so that they are aware of their rights and choices at all times.

### Intervention

2.7

#### Control group: standard treatment group

2.7.1

Participants assigned to the control group will receive routine medical care provided by a multidisciplinary medical team, which follows established clinical guidelines for the management of COPD. Standard nursing includes: (1) regular outpatient visits, treatment plans formulated by physicians, and clinical evaluations; (2) Follow up at predetermined intervals to monitor the condition; (3) Conduct routine diagnostic evaluation based on clinical indications (such as lung function testing and measurement of basic physiological indicators); (4) Provide traditional health education during clinical contact, with a focus on disease awareness, medication adherence, and lifestyle recommendations; (5) If necessary, refer to relevant specialist physicians.

The control group participants will not be able to use the AI-HEALS system, nor will they be able to access AI based digital health education, personalized reminders, or interactive self-management support provided through the WeChat platform. Except for the lack of AI-HEALS intervention measures, the two groups remained consistent in other aspects of routine clinical care.

#### Intervention group: standard treatment + AI-HEALS-based COPD online health education program

2.7.2

In accordance with settings for earlier RCTs in COPD, this trial used a 3-months intervention. Throughout these 3 months, AI-HEALS will administer the intervention to the intervention arm via the “COPD Management Expert” WeChat application. Public health professionals, clinicians, clinical nurses, psychologists, and statistician analysts make up the intervention team with their individual sets of expertise contributing to intervention development. Their intervention program is based on four main components which are as follows (Figure 2):

**FIGURE 2 F2:**
[figure not shown]
Study design and technical pathway of the AI-HEALS. All participants receive standard physician-led routine care. Participants in the intervention group additionally receive a 3-months AI-HEALS–based online health education program delivered via WeChat, which includes a COPD knowledge-based question-answering system, monitoring of physiological and lifestyle indicators, individualized reminders, and automated COPD education to support self-management and treatment adherence.

Chronic obstructive pulmonary disease Knowledge-based Question Answering System (KBQA): the COPD KBQA is designed to support patient health education by providing accurate and guideline-concordant information related to COPD. The system is implemented as a frequently asked questions (FAQ) robot embedded within the WeChat platform (Figure 3), enabling patients to conveniently access COPD-related educational content through text or voice interaction. A structured and self-developed COPD knowledge base underpins the KBQA system. The knowledge base was constructed based on established clinical guidelines and evidence-based literature and covers key domains including disease concepts, etiology, symptoms, pharmacological and non-pharmacological treatments, medication use, daily self-management strategies, dietary recommendations, and appropriate physical activity. To ensure clinical accuracy and safety, the content of the knowledge base is reviewed and periodically updated by clinical experts with experience in COPD management. The KBQA system integrates this curated knowledge base with Doubao, a ByteDance-developed large language model (LLM), which serves as a natural language interface to facilitate patient–system interaction. The LLM was not fine-tuned with COPD-specific data. Instead, it is configured to generate responses grounded in the predefined COPD knowledge base, thereby constraining outputs to validated educational content rather than unrestricted free-text generation. This design aims to enhance the reliability and safety of the information provided while maintaining conversational usability. To promote sustained engagement, the system automatically recommends three context-relevant follow-up questions after each user query. User interaction data, including question content, access frequency, and usage time, are securely logged at the backend for system optimization purposes. These data are analyzed to identify common informational needs and to guide iterative refinement of the knowledge base under expert supervision. The KBQA system is intended solely to support health education and self-management and does not provide diagnostic or treatment decision-making advice.

**FIGURE 3 F3:**
[figure not shown]
Artificial Intelligence Health Education Precision Linkage System responses to chronic obstructive pulmonary disease knowledge. Representative screenshots show text-based interactions between patients and the AI-HEALS system via the WeChat interface, illustrating guideline-based responses to common COPD self-management questions and the provision of context-relevant follow-up prompts.

Recording and Tracking Physiological Signs and Lifestyle Modifications: AI-HEALS will be utilized in this trial to encourage COPD patients to track regularly lifestyle components, such as their compliance with medications each week, their diets, and exercise. Participants will be able to enter information directly into the system, with researchers gaining instant access to recorded material via a backend interface, allowing long-term tracking and monitoring of self-management. In order to establish relevance and accuracy of data, the research team will work with families to create SMART (Specific, Measurable, Achievable, Relevant, Time-bound) plans through initial participation. Data collection will then be framed against these plans with system-generated reminders every Saturday to facilitate uploading of information. This will enable overall evaluation of intervention effects on patients’ everyday life as well as ensuring that data is aligned with individual-family-related targets.

Individualized Reminder Function: to facilitate treatment compliance, the AI-HEALS system will provide an individualized reminder service (Figure 4). Participants can conveniently set reminders on specific tasks, e.g., taking medicine and exercise. Once reminders are programmed, notifications will be sent by the system at designated times. Through this reminder function, patients are expected to comply strictly with medical treatment advice, ensure long-term continuation of healthful behaviors, and ultimately help them better manage COPD.

**FIGURE 4 F4:**
[figure not shown]
Artificial Intelligence Health Education Precision Linkage System. **(A)** Voice interaction; **(B)** Reminder and record features. Panel **(A)** demonstrates voice-based interaction for accessing COPD health education content. Panel **(B)** illustrates automated reminders and behavior-recording functions, such as exercise reminders and confirmation of completed activities, designed to support long-term self-management.

Automated Family-Centric COPD Education Articles: in addition, there will also be an automated system for dispensing education articles. COPD patients will receive one to three COPD management-related articles every week that cover different topics. Examples of topics include nutrition tips on which foods are good for COPD patients to eat and which foods to avoid, exercise tips that provide appropriate levels of physical activity, and precise drug information such as optimal administration procedures and which expected side effects to watch for. Educational content will be distributed in a tailored way to address each participant’s individual requirements based on their engagement with the system, such as the types of questions submitted, frequency of visits, and areas of increased interest. To ensure optimum use of information dissemination, background information, such as number of documents read by participants, their preference of type of documents, and length of time spent on each document, will be continuously monitored. Frequency of distribution and content will be optimized based on these findings.

Lastly, in the context of this research, maintaining participants’ privacy and guaranteeing security of their information in their engagements with the AI-HEALS system is imperative. Patient information that is collected using the AI-HEALS system will be handled under maximum confidentiality and will only be utilized for research. Each of our members in the research team is under binding privacy and confidentiality agreements, which means that they are bound by law and ethics to protect sensitive information from participants. In addition, study participants are entitled to withdraw from participation unconditionally at any point without any explanation. This right ensures that participants’ autonomy is respected and that no participant is made to proceed with their participation. Finally, all intervention-related adverse events will be carefully documented and reported in strict compliance with local law and in accordance with standard protocols.

